## B9 Provide an explanation in lay language outlining each methodology of the study, as identified in question B8.

The development process of EPO Feeding program is according to MRC framework [49], including systematic reviews, qualitative interviews, cross-sectional study, and feasibility and acceptability RCT. In this study, we will conduct the feasibility and acceptability RCT. The development process for this feasibility trial is uploaded in Appendix Figure 1.

### Recruitment and consent process:

The recruitment and consent process for participants is the same as outlined in section C4 of this form. (Appendix figure 2)

### Participant Eligibility Criteria:

The inclusion and exclusion criteria for participants are the same as outlined in sections C2a and C2b of this form.

### Study design

EPO Feeding program involves several components, targeting optimizing parental feeding practices in China. A two-arm feasibility and acceptability RCT with three repeated measures will be used to test the feasibility and acceptability of EPO Feeding program. After baseline assessment, parents who are responsible for their child's eating behaviors and family food environment will be randomly assigned to one of the two conditions: one experimental group (EPO Feeding program and standard care) and one control group (standard care). The four weekly modules of the multicomponent intervention curriculum include four modules. After finishing the program, parents complete the measures immediately and one-month follow-up. Semi-structured interviews will be conducted with parents to support the process evaluation of the 4-week intervention program after the intervention.

### Randomization

The randomization will be performed by an independent researcher (XXW) not connected with either participant recruitment or data collection. After completing the baseline assessment, parents will be randomized and allocated to one of the conditions through a concealed computerized random number generator by randomization.com, with an equal allocation ratio (1:1). Selection bias will be minimized by ensuring all participants eligible and recruited have equal opportunity of being allocated to each study group and follow-up completed. Due to the nature of the study, only the research members who collect and analyze the data from participants can be masked to the randomization. At the follow-up data collection time points, child height and weight measurements, and follow-up questionnaires will be taken and distributed by a trained kindergarten healthcare staff blinded to group allocation. Unmasking will not occur until databases are closed, and the main analysis has been completed.

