### Intervention group

Participants in the intervention group will receive EPO Feeding program and standard care. The EPO Feeding program is a 4-module intervention program focused on optimizing parental feeding practices. The components and contents of the EPO Feeding program are presented in Appendix 6. Two healthcare professionals in the Department of Child Health in the local maternal and child health hospital will be trained to deliver the EPO Feeding program. Before each module, they will pre-present the module to the researcher (JW) to ensure their presentation is in accordance with the EPO Feeding intervention manual via VooV Meeting, which will be recorded and sent to parents in the control group after all follow-ups. Considering the effectiveness and cost-effectiveness of the intervention [1], we will divide participants in the intervention group into two groups (15-18 parents per group) to attend the modules separately. Each weekly module will last 45-60 min in the kindergarten classroom, incorporating lesson/session (i.e., slides shows and handouts), group discussion, uptake of key messages, supplementary materials (e.g., stories, key messages and learning videos) to improve the acquisition of participants' knowledge, skills, and behaviors. Each module will take place twice every week (Friday: 12.30-13.30 PM; Saturday: 09.00-10.00 AM) at the kindergarten premises after receiving approval from the gatekeeper. Parents in the intervention group can choose one regular time to attend the module every week. After each module, homework activities will be assigned to participants to help reinforce their knowledge, skills, and behaviors. Participants will receive weekly messages via WeChat reminding them to attend the module with brief information. On the other hand, a WeChat group will be built to facilitate parental involvement, learning, and communication. The WeChat group will be monitored by two healthcare professionals in the areas of child health and nutrition. You can share your feelings, experiences, ideas or practices relevant to each module in the WeChat group. It is

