**(1) Parents in this feasibility trial (including parents in the intervention and control group)**

As this is a feasibility study, a formal sample size calculation for between-group comparisons of a primary outcome is not appropriate. A sample size of between 25 and 50 is considered reasonable in a feasibility study, to be able to establish feasibility, estimate the difference in retention rates with accuracy, and attain an appropriate standardized effect size (0.15-0.3) [1, 2]. The target recruitment for this feasibility RCT will be 70 (i.e., 35 participants per group), allowing for a 20% loss to follow-up rate and for at least 56 participants to complete the study.

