Parents of preschool children will be recruited from two kindergartens in Yangzhou, China after getting the approval of each gatekeeper (head of kindergarten). Participants will be recruited via posters and take-home letters, providing details about the study. Information about the program and how to participate in the study will be also shared through common social networks (i.e., parent meetings). Specifically, after getting the approval, posters inviting caregivers and the contact details of the principal investigator (JW) will be displayed on the main notice boards, and waiting areas at the kindergartens. The healthcare staff who are not the kindergarten teachers in each class will make an announcement for this study and distribute the take-home letters, participant information sheet (PIS) and ineligibility statement to parents in the parent meeting.

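### Parents come from two kindergartens, but the stated 1:1 allocation is not stratified by kindergarten and the model does not name it as a covariate, which leaves avoidable noise in the exploratory comparisons.

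*Protocol*

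**What the plan says.** Section C4 of the Protocol names the sites: "Parents of preschool children will be recruited from two kindergartens in Yangzhou, China". Section B6 gives the same two-kindergarten setting.

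Section B9, Randomization, sets the unit and timing: "After completing the baseline assessment, parents will be randomized and allocated to one of the conditions". The tool is a "concealed computerized random number generator by randomization.com, with an equal allocation ratio (1:1"), run by a researcher independent of recruitment and data collection. No stratum, block or minimisation factor is stated there or anywhere else in the document.

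Section C1 sets the size: "The target recruitment for this feasibility RCT will be 70 (i.e., 35 participants per group), allowing for a 20% loss to follow-up rate". The stated aim is a total of no fewer than 56 completers. The section adds that "a formal sample size calculation for between-group comparisons of a primary outcome is not appropriate".

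Section B9, Quantitative data analysis, puts treatment condition in the linear mixed model as the fixed factor. It gives parental education and the child's sex and age as examples of covariates. Kindergarten is not among them. The same section addresses the primary objectives descriptively and calls the analysis of the secondary objectives exploratory.

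**The concern.** Kindergarten is known for every parent before allocation. It is the unit through which parents are recruited, and the note in section C4 says that kindergarten health staff look after the children's meals and the weight and height assessments. It could therefore plausibly be related to the secondary outcomes of feeding practices, child eating and BMI-Z.

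A 1:1 ratio balances the number of parents per arm. It does not balance where they come from. With 70 parents and two sites, the kindergarten mix of the arms can drift apart by chance. If outcomes differ between the kindergartens and the model has no site term, that drift goes into the observed arm difference. At stake is the precision and readability of a small between-arm comparison that is meant to inform a full trial.

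**Working it through.** **The plan's own figure.** 56 completers with 20% loss: 56 / (1 − 0.20) = 70, or 35 per arm. The stated target reproduces exactly.

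**Inputs.** From the Protocol: N = 70 and 35 per arm (C1), two kindergartens (C4), 1:1 allocation with no stated stratum (B9). Assumed: the number K of parents from kindergarten A. I use K = 35, 45 and 20, that is, splits of 35/35, 45/25 and 50/20 (K = 20 is the smaller site of the last split).

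**Formula.** Hold both arms at 35, which is the case most favourable to the plan, and do not stratify. Let X be the number of parents from kindergarten A in the intervention arm. Then X is hypergeometric (population 70, K from A, 35 drawn). The difference in kindergarten share between arms is

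d = X/35 − (K − X)/35 = (2X − K)/35.

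So |d| ≥ 0.20 means |2X − K| ≥ 7, and |d| ≥ 0.10 means |2X − K| ≥ 3.5.

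| Assumed split | Values of X giving \|d\| ≥ 0.20 | P(\|d\| ≥ 0.20) | Values of X giving \|d\| ≥ 0.10 | P(\|d\| ≥ 0.10) |
|---|---|---|---|---|
| 35/35 (K = 35) | ≤ 14 or ≥ 21 | 0.151 | ≤ 15 or ≥ 20 | 0.339 |
| 45/25 (K = 45) | ≤ 19 or ≥ 26 | 0.134 | ≤ 20 or ≥ 25 | 0.318 |
| 50/20 (K = 20) | ≤ 6 or ≥ 14 | 0.063 | ≤ 8 or ≥ 12 | 0.428 |

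X is a whole number, so the first value that crosses a threshold differs by row. At K = 20 the smallest qualifying differences are 8/35 = 0.229 and 4/35 = 0.114. At K = 35 and 45 they are 7/35 = 0.200 and 5/35 = 0.143. That is why the two probability columns do not move together.

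**What an imbalance does to an estimate.** The shift in the arm difference is the share imbalance times the outcome difference between kindergartens. The Protocol gives no between-kindergarten difference. Assuming 0.2 to 0.5 SD, a 20-point imbalance shifts the unadjusted arm difference by 0.20 × 0.2 = 0.04 SD to 0.20 × 0.5 = 0.10 SD. For scale, if the 56 completers split evenly at 28 per arm, the standard error of a simple mean difference is √(2/28) = 0.27 SD.

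**After the change.** With permuted blocks of at most 4 (assumed) in each kindergarten, the arms can differ by at most 2 within a kindergarten and 4 overall. The totals stay between 33:37 and 37:33, and the kindergarten mix is close to equal by construction.

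**The case against.** The best case for leaving the plan alone has four parts.

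- **Chance imbalance does not bias a randomised comparison.** This stands. The expected imbalance is zero, and the cost is precision and ease of interpretation in one small sample. The shift worked out above is also well below the standard error.
- **The comparison is exploratory.** This stands too. The primary objectives are descriptive and section C1 disclaims a formal calculation, so nothing confirmatory depends on the point.
- **The covariate list is open, and details can be settled later.** This stands in part. The covariates are given as examples, so kindergarten is not excluded from the model. Strata are different: they must be fixed before the first allocation, and an analysis plan cannot restore them afterwards.
- **No site difference is documented.** This stands. Section C6b divides the three healthcare staff by task and not by kindergarten, so the text does not show that measurement differs between sites. Nor does it say that meals differ.

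Three stronger readings are tempting, and the document does not support them.

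- A reader might infer simple, unblocked randomisation and conclude that "35 participants per group" is not secured. Under simple 1:1 allocation of 70, exactly 35:35 would occur with probability 0.095. But the list type is not stated, and a balanced 70-long list is equally compatible with the text.
- A reader might infer a target of 28 completers per arm that uneven arms would break. Section C1 gives only the total of 56.
- A reader might blame the allocation for the plan to divide the intervention arm "into two groups (15-18 parents per group"). That range conflicts mainly with the free choice of Friday or Saturday allowed in the same section. With exactly 35 parents choosing at 50/50 (assumed), both sessions fall in the range only 26% of the time. Stratified blocks would not change this.

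**Conclusion.** The point holds as a minor design improvement. Kindergarten is available before randomisation, is not a stated stratum and is not a named covariate. With arms fixed at 35/35, a kindergarten imbalance of 20 points or more has probability about 0.06 to 0.15, and one of 10 points or more about 0.32 to 0.43, over assumed splits from 35/35 to 50/20. A balanced overall list would not remove this; stratification would.

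The consequence is avoidable noise in the exploratory comparisons of feeding, eating and BMI-Z. Its size depends on a between-kindergarten difference that the Protocol does not give, and it vanishes if the kindergartens do not differ. The design is not biased by it, and the descriptive feasibility and acceptability objectives are unaffected.

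**What to change.** In section B9, Randomization, state that the independent researcher generates one permuted-block 1:1 list per kindergarten, with varied block sizes, and conceals the lists and block sizes from those who recruit and collect data. In section B9, Quantitative data analysis, name kindergarten as a fixed covariate in the linear mixed models.

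The cost is one additional list, one model term and slight predictability within blocks, which varied and concealed block sizes limit. No extra participants or staff are needed. This change does not settle the session sizes; the group range and the free choice of session in section B9, Intervention group, have to be reconciled separately.

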Research on using qualitative methods for feasibility and acceptability RCT will be likely of particular importance in refining understanding of how the intervention works and facilitating ongoing adaptation of intervention and evaluation design in preparation for a full trial. Thus, this study will nest a process evaluation, including semi-structured interviews and observation of modules, which aim to extend an in-depth understanding EPO Feeding intervention program for this feasibility and acceptability trial.

- 1) Semi-structured interviews will be conducted for participants and healthcare professionals who delivered the intervention modules. A topic guide (Appendix 1: interview topic guide) was developed by the research team to address the research questions.
- 2) The researcher (JW) will observe each module, which aims to expand the immediate response and feedback for each module

and to assess the level of intervention fidelity. The researcher (JW) will also make fieldnotes about the module delivery and response to the modules provided on the program, barriers and enablers of the program completion, participants' task engagement, and its overall structure, delivery, and content of the program (Appendix 2: Observation checklist).

3) All modules will be video/audio recorded by a facilitator and checked by two researchers (XXW and JW) to rate against the fidelity checklists and ensure modules are delivered as intended (Appendix 3: Fidelity checklist).

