**C6b Outline who the gatekeeper is and how they will be used to facilitate recruitment.**

*Please note: Participants must only be approached once appropriate gatekeeper permission has been obtained.*

The gatekeeper is each head of the kindergarten from two kindergartens in Yangzhou, China.

First, we will obtain permission from each gatekeeper at two kindergartens to display the study invitation posters on notice boards and waiting areas. We will also ask three kindergarten healthcare staff to distribute the take-home letters, participant information sheet (PIS) and ineligibility statement at the most recent parent-teacher conference.

Second, we will request permission to recruit three kindergarten healthcare staff who do not have regular contact with parents. These healthcare staff will make an announcement for this study and distribute the take-home letters, participant information sheet (PIS) and ineligibility statement in the parent meeting. They will also announce that participation is completely voluntary and non-participation will not disadvantage them and their child (e.g., education, care) in any way. One of these healthcare staff will be responsible for distributing and collecting consent forms, baseline and follow-up questionnaires (blindness for group allocation). The second healthcare staff will assess these preschool children weight and height at each time point based on the student ID on the baseline questionnaire provided by their parents after obtaining the participants' consent form (blindness for group allocation). The third healthcare staff will send text messages of child's actual weight status to parents in the intervention (not blindness for group allocation). This work is voluntary because it will take place during their usual working hours. We will let kindergarten healthcare staff know that it is not mandatory to distribute/collect questionnaires and measure child weight and height. If they are unavailable to support the project, it will not affect them in any way.

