Next, we will ask permission to place a box in the kindergarten's waiting areas for five working days (8.00 AM-5.00 PM every day) three times after the kindergarten healthcare staff distribute the consent form and baseline questionnaires (the first time), questionnaires/survey immediately after intervention (the second time) and questionnaires one-month follow-up (the third time) within a regular date (around two working days each time) at the kindergarten's waiting areas (4.30-5.30 PM off-school period) so that parents can return the consent form and questionnaires. This healthcare staff will check the box every day and collect the returned consent form and questionnaires.

Finally, we will request permission from gatekeepers at kindergartens to book/provide a kindergarten conference room/other available premise for intervention modules and semi-structured interviews (process evaluation).

The gatekeeper will not be aware of who participates in the whole process.

-We will also obtain permission from the parents of children that the kindergarten healthcare staff will assess their child's height and weight at each time point via the student ID they write on the questionnaire after receiving their consent form.

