### D4a Please explain how you will ensure participants remain completely anonymous in the final report or any other research output/s.

Data will be processed under the terms of UK data protection law (including the UK General Data Protection Regulation (UK GDPR) and the Data Protection Act 2018). King's College London (KCL) is the sponsor for this study. The research team will be using information from the participants in order to undertake this study and will act as the data controller for this study. This means that the researcher is responsible for looking after the participants' information and using it properly.

After completing this trial, all the identifying information (i.e., preschool child student ID number and participants' contact details) will be removed. During the data analysis, only pseudonymized data will be shared with research team members. The data will no longer be identifiable by anyone after JW's thesis submission. The pseudonymized data (information from this study) will be retained for 7 years according to the KCL regulation.

All information collected during the study will be kept strictly confidential and will be stored securely and handled according to data protection guidelines. Any information about you and your child will have personal details (i.e., child student ID number and contact details) removed when shared within the research team so that no one can be recognized from it. Regarding the child's weight and height records, JW will use software to calculate child's BMI-Z score accordingly and then share BMI Z-score with the research team. Likewise, other information which may be identified will be deidentified by JW and then be shared within the research team.

Only JW will have access to the identifiable information and the entire research data. Personal information (i.e., preschool child student ID and contact detail) will be kept separately from depersonalized data, and field and kept in a locked cabinet in JW's office at King's College London. This cabinet will be situated in a locked room, for which only JW has a key. While still in China for data collection, all hard copies of documents and data will be stored in a locked cabinet in JW's place of residence at Yangzhou –Jiangsu, China, and only JW will have a key to the cabinet.

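### The masking statement cannot hold for the principal researcher, no masked analyst is identified, and the programme survey may unmask the questionnaire distributor

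*Protocol*

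**What the plan says.** Under Randomization (B9), the protocol limits masking to one group: "only the research members who collect and analyze the data from participants can be masked to the randomization". It then says, without exception, that "Unmasking will not occur until databases are closed, and the main analysis has been completed". For outcome collection it adds that "follow-up questionnaires will be taken and distributed by a trained kindergarten healthcare staff blinded to group allocation".

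Other sections assign the work:

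- **B8, process evaluation.** The principal researcher "will observe each module, which aims to expand the immediate response and feedback", keeps fieldnotes and, with the researcher who randomises, rates the module recordings for fidelity.
- **B9, Qualitative data.** The principal researcher messages parents who drop out and asks them for an interview.
- **D4a, repeated in E8a.** Only the principal researcher "will have access to the identifiable information and the entire research data". The same person removes identifiers, calculates the BMI Z-score and passes de-identified data to the team.
- **C6b.** Three kindergarten staff have separate duties. One is responsible for "distributing and collecting consent forms, baseline and follow-up questionnaires (blindness for group allocation". A second, also described as blind, measures height and weight. A third, described as not blind, sends the weight-status messages. The second distribution round is described as "questionnaires/survey immediately after intervention (the second time".

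**The concern.** Only the intervention arm attends modules. Anyone who sits in on all of them knows from the first week which parents were allocated to the programme. If that person also controls linkage, de-identification, derivation and release of the dataset, then data handling takes place with knowledge of allocation while the protocol says masking is intact.

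The survey raises a second, smaller problem. A form that asks parents to rate the programme makes sense only for those who received it. A staff member who hands it to some parents and not others can infer allocation, with one questionnaire round still to come.

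The credibility of the between-group comparisons is at stake. They are exploratory, but they are tested at P < 0.05 and would inform a full trial. A report that repeated the masking statement would claim a protection that the procedures do not provide.

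**Working it through.** No arithmetic underlies the masking claim, so the check sets the sections side by side.

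1. **Does the principal researcher learn allocation?** B8 has this person observe every module. In B9, the Intervention group section provides the modules, while the Control group section gives control parents standard care and offers programme material only after the one-month follow-up. Observing a module therefore identifies intervention parents. The same person screened the parents (C2c, C4) and contacts those who drop out (B9, Qualitative data).

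2. **Is this person among those who collect and analyse data?** The observation notes and fidelity ratings are collected data. D4a and E8a add sole access to the full dataset, de-identification and calculation of the BMI Z-score. C10 adds removal of a withdrawing parent's data by the child's student number. All of this comes before or during analysis.

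3. **Comparison with the claim.** Steps 1 and 2 place one person both inside the group said to be masked and inside the intervention sessions. The statement in Randomization is unqualified, so it is false for that person.

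4. **Is a masked analyst identified elsewhere?** The other named researcher generates the allocation (Randomization), rates module recordings (B8) and indexes interview transcripts (B9, Qualitative data analysis). The two healthcare professionals on the team deliver the modules. D4a says pseudonymised data are shared with team members during analysis. A masked analyst is therefore possible but is not specified.

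5. **The survey.**
   - B8, Acceptability: the questions ask parents to rate the programme.
   - C6b: it goes out in the round directly after the intervention (T1), handled by the staff member described as blind.
   - B9, Control group: control parents have had none of the programme at that point.
   - Recipients: not stated anywhere in the protocol.
   - If it goes only to intervention parents, the distributor can infer the arm of up to 70 / 2 = 35 parents (C1 target, 1:1 allocation) before the one-month round (T2). The survey's anonymity does not prevent this, because the disclosure happens at hand-out.
   - If it goes to every parent, hand-out reveals nothing, but control parents are asked to rate something they never received.

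6. **What is not contradicted.** C6b separates the person who measures height and weight from the unblinded message sender and from the principal researcher. No procedure defeats the masking of that measurement.

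**The case against.** The best defence is that the protocol never says the principal researcher runs the quantitative analysis. Who analyses, and on what coding, is often left to a statistical analysis plan, and the Data analysis section already names the tests and models. This stands in part. A reader might infer that the analyst is shown to be unmasked, or that model choice is unprotected; the protocol does not support either. What remains is the unqualified statement, which the principal researcher's documented duties contradict whoever fits the models.

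Other tempting inferences also go too far:

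- **Parent-reported outcomes.** There are 6 feeding, 2 perception, 2 competence and 5 eating-behaviour measures plus BMI Z-score, 16 in all, of which 15 rest on parents who know their arm. This does not measure the error. Randomization already implies that parents are unmasked, and the count would be the same with perfect analyst masking.
- **BMI Z-score.** It comes from standard software applied to measurements by masked staff, so there is little room for discretion. Its derivation shows the principal researcher's role, not a likely bias.
- **The randomiser.** Later rating and indexing do not undermine allocation concealment. They only make this person unsuitable as a masked analyst.
- **The survey.** Disclosure is conditional on the recipients. The bias route is also weak, since parents complete the forms themselves and return them to a box, and the distributor is not described as scoring anything.

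Finally, the primary objectives are descriptive feasibility measures that require knowing who attended. Masking matters little to them, which limits the consequence.

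**Conclusion.** The masking statement is wrong as written for one person, and that person controls the whole dataset. This follows directly from Randomization read against B8, D4a and E8a, and needs no assumption about who analyses. Masking of the main analysis is unsecured rather than shown to be absent.

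The survey problem rests on the assumption that only intervention parents receive the form. Under it, up to 35 allocations become visible to the questionnaire distributor before the last round; if all parents receive it, none do. The protocol should settle which applies.

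The primary feasibility results are little affected. The exploratory between-group comparisons are where the correction matters, and it is worth making because it costs little. No numerical bias can be derived from the protocol, and none is claimed.

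**What to change.** - **Restate masking in Randomization.** Say that parents, those who deliver the modules, the principal researcher and the randomiser are not masked, and neither is the staff member who sends weight messages, as C6b already says. Say that the kindergarten staff who measure height and weight and who handle questionnaires are masked.
- **Secure the main comparison.** Have a team member without module contact run the prespecified main intention-to-treat comparison on data coded A/B, with no attendance variables. Release the codes once those results are fixed and before the completers analysis, which needs module counts. If the team has no such member, drop the claim that the analyst is masked.
- **Take the survey out of the masked channel.** State who receives it. Give it out at the last module or by WeChat link, or put it in identical sealed envelopes that go to every parent. With envelopes, its return should be sealed too, because the same distributor empties the box.

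The cost is a change of wording and a small change in handling. Some analysis work moves to another person, and the completers analysis runs later. A survey given out only at the last module would miss absent parents; the link or envelopes avoid this.
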